### Secondary hypotheses

1. Children with cancer and CVL-dysfunction have an increased prevalence of infection compared to those without CVL-dysfunction. Presence of both CVL-dysfunction and infection increases the risk of TE in children with cancer.

2. Children with cancer and CVL-dysfunction have decreased OS and EFS compared to those without CVL-dysfunction.

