### Secondary aims

In children receiving therapy for cancer,

1. To compare the prevalence of infection at any site in children with or without CVL-dysfunction

2. To compare the five-year OS and EFS in children with or without CVL-dysfunction

3. To delineate the relationship of CVL-dysfunction, infection and TE

4. To evaluate the impact of different CVL-related (type, insertion techniques, care guidelines) and patient-related (age, height, body mass index) factors on the development of CVL-dysfunction, TE and infection

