#### Exclusion criteria

1. Patients with relapsed cancer since they would have had previous exposure to CVL

2. Age > 18 years at cancer diagnosis since majority are treated at the adult facilities

3. Absence of CVL

4. Diagnosis of CVL-dysfunction prior to study enrollment

5. Patients on anticoagulation therapy or prophylaxis

6. Unable or unwilling to provide written informed consent (and/or assent) for the proposed study

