#### Definitions

1. CVL-dysfunction: Persistent or recurrent difficulty in blood draw and/or infusion of at least one CVL lumen with or without the need for instillation of tissue plasminogen activator (tPA) documented on two or more occasions. For a multi-lumen CVL, difficulty in infusion or withdrawal of the same lumen for ≥ 2 occasions is required to fulfill the criteria of dysfunction.

2. Symptomatic thromboembolism: total or partial occlusion of one or more vessels objectively confirmed by at least one radiological diagnostic method prompted by typical clinical symptoms. CVL-related DVT: total or partial occlusion of vessel in which CVL is placed and/or right atrial TE.

3. Infection: Published guidelines will be used for diagnosis of CVL infection [47,48]. In addition a patient will be diagnosed with *infection* in any of the following situations:

For the purpose of this study patients with suspected or proven viral (e.g. influenza, chicken-pox) as well as mycoplasma infection will not be categorized as “infected”.

a. Septic shock requiring Pediatric Intensive Care Unit (PICU) admission with or without microbiological proof.

b. Positive blood culture collected from CVL and/or peripheral vein requiring intravenous (IV) antibacterial and/or antifungal therapy beyond 48 hours.

c. Invasive fungal (including candidial) infection defined as positive blood culture or positive culture from any other site (except oral or perianal candidiasis), radiological documented probable infection requiring systemic antifungal therapy and/or histopathological evidence of fungal infection (e.g. documentation of fungal hyphae on biopsy)

d. Clinically documented infection (e.g. CVL site infection, tunnel track infection, cellulitis, abscess formation at any site, typhlitis), with or without microbiological proof, requiring antibacterial or antifungal therapy beyond 48 hours. Minor infections like suspected otitis media, streptococcal throat infection will be excluded.

e. Persistent and/or recurrent fever of unknown origin requiring antibiotics therapy beyond 7 days.

4. Event: recurrence of cancer, SMN or death due to any cause.

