#### Study follow-up and study duration

This study will require no visits above and beyond those required for the clinical care of the patient. After initial hospitalization for evaluation and therapy for cancer, all patients are seen frequently (either weekly or monthly) at the outpatient clinics as part of their routine clinical care. Patients will be monitored for infection, disease progression or recurrence, or SMN. After completion of therapy patients are followed life-long according to the “After-Care-Guidelines” recommended by POGO.

Patient enrollment will occur until the required sample size is achieved. We anticipate that the required patient population will be enrolled during first two and half years of the study. Patients will be followed for the development of symptomatic TE until the completion of cancer therapy and final removal of CVL which occurs within 6–12 weeks post completion of therapy. Thereafter overall outcome data regarding continued remission, recurrence of cancer, SMN or death will be collected for each patient every six months for a total period of five years from the initial diagnosis.

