##### Measurement of the exposure (i.e. CVL-dysfunction)

To avoid recall bias in recording CVL-dysfunction, CVL-access information will be collected and recorded prospectively. Currently on the the inpatient unit, every time the CVL is accessed, the nurse accessing the CVL completes the CVL checklist and records any problems in blood-draw, infusion or need for tPA. Similar checklist will be filled out for patients’ outpatient visits as well as emergency room visits, if any. These checklists will be collected and reviewed by the study staff at regular intervals In addition, during the regular clinic visit patients (or care givers) will be asked about the functioning of CVL and any problems encountered and their responses documented. We believe that combination of prospective documentation by nursing staff and patient recall will capture all the events of CVL-dysfunction. The patient will be categorized as “exposed” once the patient has met the criteria for CVL-dysfunction.

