##### Analysis plan

The analysis and reporting of the study will be performed in accordance with the STROBE Statement [50]. The primary outcome is a binary variable- symptomatic TE (presence/absence) as well as a continuous variable (time to event). Independent variables include: age, number of catheter days and time to CVL-dysfunction as continuous variables and, gender (male/female), cancer type, CVL-dysfunction (presence/absence), symptomatic TE (presence/absence), infection (presence/absence) as categorical variables. The process of participant recruitment and retention will be summarized using a flow diagram. Analysis results of participant recruitment and retention will be summarized using descriptive summary measures: mean (standard deviation) or median (minimum-maximum) for continuous variables; and number (percent) for categorical variables. We will use logistic regression analysis to determine the factors that can best discriminate between the two patient groups (i.e. those with and without TE). The list of potential factors is determined *a priori* and includes age of the patient at the time of diagnosis of cancer, cancer type; CVL-dysfunction (presence/absence), infection (presence/absence) and CVL type (internal/external). Univariate analyses will be performed to determine which variables to include in the multivariable models using the criterion of alpha = 0.20. Initially, we will use complete case analysis (i.e. do the analysis without taking missing data into account) and then repeat the analyses with missing data handled by multiple imputation technique [51-53].

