For regression models, we will report the OR (for logistic regression), corresponding standard error, 95% confidence intervals and associated p-values. We will report P-values to 3 decimal places with p-values less than 0.001 reported as p<0.001. For all tests, we will use alpha =0.05 level of significance. Examination of residuals will provide an assessment of model assumptions for regression analyses. Goodnees-of-fit for the models will be performed using appropriate Hosmer-Lemeshov tests. For multivariable regression analysis, we anticipate multicolinearity [54]. We will assess colinearity using the variance inflation factor (VIF) which measures the extent to which the variance of the model coefficients will be inflated (because of the correlation of the variable with other predictor variables) if that variable is included in the model. Variables with VIF >10 will be considered colinear and will be excluded from the analysis [55].

The discriminant performance of the model will be evaluated using sensitivity, specificity and the area under the ROC – receiver operating characteristic curve. We will use bootstrapping approach to internally validate the model. We will compare the performance characteristics (i.e. sensitivity, specificity, area under the ROC curve, etc) between the original model and the bootstrap model. OS and EFS will be estimated using Cox-regression which will allow for adjustment of confounding variables. Hazard ratio (HR) will be calculated using log-rank method.

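### OS and EFS are set up as an ever-versus-never comparison of CVL-dysfunction, although dysfunction arises during follow-up: harm on OS is attenuated, and the direction of the EFS bias is left open

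*Protocol article*

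**What the plan says.** All places are in the protocol article.

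- **Aim and hypothesis.** Secondary aims, item 2: "To compare the five-year OS and EFS in children with or without CVL-dysfunction". Secondary hypotheses, item 2: "Children with cancer and CVL-dysfunction have decreased OS and EFS compared to those without CVL-dysfunction".
- **Follow-up.** Study follow-up and study duration: outcome data are collected "every six months for a total period of five years from the initial diagnosis".
- **Exposure at entry.** Exclusion criteria, item 4: "Diagnosis of CVL-dysfunction prior to study enrollment". Under Recruitment and consent process, families are approached before line placement or within two weeks of it.
- **Exposure during follow-up.** Definitions, item 1, requires difficulty "documented on two or more occasions". Measurement of the exposure classes a child as exposed "once the patient has met the criteria for CVL-dysfunction".
- **Coding.** Analysis plan: "CVL-dysfunction (presence/absence), symptomatic TE (presence/absence), infection (presence/absence) as categorical variables". The same list has time to CVL-dysfunction as a continuous independent variable.
- **Model.** Analysis plan: "OS and EFS will be estimated using Cox-regression which will allow for adjustment of confounding variables". The next sentence takes the hazard ratio from the log-rank method. No time-dependent term, landmark or delayed entry is mentioned.

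**The concern.** A child can enter the dysfunction group only by staying alive, with a line, until the second documented occasion. If groups are fixed as ever or never and the clock starts before that occasion, two errors follow for OS:

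1. Survival time before qualifying cannot contain a death, but it is credited to the dysfunction group.
2. A child who would have developed dysfunction but dies first is counted as never exposed.

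Both lower the hazard ratio. Covariate adjustment, the only safeguard the Analysis plan names for these endpoints, does not remove either error. The hypothesis is that dysfunction worsens survival, so the bias works against detecting what the aim seeks.

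The article does not name the time origin of the Cox model. Diagnosis is an inference from the five-year aim and the follow-up section. Starting at enrolment or line insertion would leave the same problem, because dysfunction still arises later.

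For EFS there is a second path. If dysfunction first met after a recurrence is also counted, children who have already had an event move into the exposed group, which pushes the hazard ratio towards harm.

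**Working it through.** **Figure to reproduce.** The article gives no event count, effect size or power for OS or EFS. The only usable planning figure is the exposure split under Sample size: 450 × 0.20 = 90 exposed and 360 unexposed.

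**Assumptions not in the documents.** Five-year survival without dysfunction of 80% (the Background cites cure rates above 80%; 70% gave nearly the same hazard ratios), the onset distribution of dysfunction, and the shape of the mortality hazard.

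**Hand check for OS, true hazard ratio 1.0.** Take 100 children, 20 destined for dysfunction, a constant hazard, and onset at 1.25 years (the mean of a uniform distribution over 2.5 years).

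- Hazard: −ln(0.80)/5 = 0.04463 per year.
- Child who qualifies: probability of death from 1.25 to 5 years = 1 − exp(−0.04463 × 3.75) = 0.1541. Person-years after onset = 0.1541/0.04463 = 3.45. Adding the immortal 1.25 years gives 4.70. Apparent rate = 0.1541/4.70 = 0.0328.
- Destined children who die first: 20 × [1 − exp(−0.04463 × 1.25)] = 1.09 deaths, with about 1.09 × 0.625 = 0.68 person-years.
- The 80 others: 16 deaths and 16/0.04463 = 358.5 person-years.
- Apparent unexposed rate: (16 + 1.09)/(358.5 + 0.68) = 0.0476.
- Ratio: 0.0328/0.0476 = 0.69, although the true value is 1.0. Counting exposed time only from onset gives 0.1541/3.45 = 0.0447, which is the true hazard apart from rounding.

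**Simulation for OS.** 400,000 to 600,000 patients per scenario; 20% to 21% destined for dysfunction; the hazard is multiplied by the true ratio only after onset; censoring at 5 years. Front-loaded means Weibull shape 0.7 in the median-onset rows and 0.6 in the uniform rows. Entries are the ever/never Cox hazard ratio; repeat runs agree to within 0.03.

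| Onset | True 1.0, constant | True 1.0, front-loaded | True 1.5, constant | True 1.5, front-loaded |
|---|---|---|---|---|
| Median 1 month | 0.97 | 0.89 | 1.44 | 1.37 |
| Median 3 months | 0.91 | 0.82 | 1.35 | 1.21 |
| Median 6 months | 0.84 | 0.73 | 1.26 | 1.08 |
| Median 12 months | 0.76 | 0.66 | 1.15 | 0.99 |
| Uniform over 1 year | 0.87 | 0.71 | 1.29 | 1.03 |
| Uniform over 2.5 years | 0.69 | 0.53 | 1.01 | 0.77 |

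In the median-onset scenarios a true ratio of 2.0 reads 1.92 down to 1.29 at 80% survival. With dysfunction as a time-dependent covariate, the same data return 0.98–1.01, 1.49–1.52 and 1.99–2.02 for true ratios of 1.0, 1.5 and 2.0.

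**EFS, true hazard ratio 1.0.** Further assumptions: 25% five-year events, 80% of them recurrences, median onset 1 to 12 months, constant or shape-0.7 hazard.

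| Share of recurred, still unexposed children who later qualify and are counted | Ever/never hazard ratio |
|---|---|
| None | 0.66 to 0.97 |
| 10% | about 1.0 to 1.3 |
| 20% | about 1.4 to 1.7 |

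The sign therefore depends on a rule that the article does not give.

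**The case against.** The strongest reply is that the biased model is partly inferred. The presence/absence coding stands in a general variable list and in the logistic model for TE; no covariate list is given for the Cox model. The article also lists time to dysfunction and makes exposure begin when the criteria are met, and both would fit a time-dependent analysis. An article may leave such detail to a fuller plan.

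Part of this stands: the time origin is not stated, and Cox regression as such is neutral on coding. But the text is not merely silent. The aim contrasts two groups, the coding is binary, and a log-rank hazard ratio in its ordinary form compares fixed groups. Time to dysfunction is undefined for children who never have it, so as an ordinary covariate it repairs nothing.

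Three stronger readings are tempting but not supported:

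- *The plan will hide or reverse a real harm on OS.* That is the far end of the range. With a median onset of 1 to 3 months and constant hazard, a true 1.5 still reads about 1.45 to 1.35. The documents do not say when dysfunction arises.
- *EFS is biased towards protection in the same way.* No passage stops the recording of dysfunction at recurrence. The section on CVL insertion refers to initial cancer therapy, but only for line details.
- *All children who die or relapse early are put in the unexposed group.* Only those who have not yet qualified are. Among children destined for dysfunction, the median-onset scenarios give about 0.5 to 8.5 such children in 450.

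**Conclusion.** The point holds. The passages together set up an ever/never comparison for an exposure acquired during follow-up.

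- **OS:** the bias is towards no harm. Under 80% survival and about 20% exposed, a true hazard ratio of 1.0 reads from about 0.97 down to about 0.5, and a true 1.5 from about 1.45 down to about 0.8. The position within that range depends on onset timing and on how early deaths fall, neither of which the documents give.
- **EFS:** the same bias applies if dysfunction after recurrence is not counted. If it is counted, the bias can run towards harm. The text does not determine the sign.

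A reader might infer a flaw that threatens the whole study. It does not: OS and EFS are a secondary aim, and the primary outcome and the sample size of 450 are unaffected by this point. It should be fixed, but it is not critical.

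**What to change.** In the Analysis plan, state that:

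1. CVL-dysfunction enters the OS and EFS Cox models as a time-dependent covariate that turns on at the second documented occasion, with the time origin named.
2. The hazard ratio comes from that model, not from a fixed-group log-rank.
3. For EFS, dysfunction first met after recurrence or second malignancy is ignored.
4. Survival curves by dysfunction status use one fixed landmark, for example 6 months from diagnosis, restricted to children still alive (OS) or event-free (EFS) at that point.

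The cost is a few sentences. The access checklists and the time-to-dysfunction variable already supply the dates, so no new data are needed, and no stated sample size changes. The drawback is that the landmark curves drop events before the landmark; the time-dependent model keeps them and should carry the inference.

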Deitcher et al., reported CVL-dysfunction in 28% children with brain tumors; children with CVL-dysfunction, but not with major TE, had a reduced overall survival [32]. Further, our results suggest that CVL-dysfunction is an independent risk factor for poor OS and EFS in children with cancer [33]. The poor outcome in children with cancer and CVL-dysfunction could be related to the interruption in therapy due to the loss of CVL or due to the associated complications like TE and infection. In addition, CVL-dysfunction may represent activation of coagulation system; a marker of poor prognosis in adults with cancer [32,33,36]. Thus, CVL-dysfunction probably reflects significant underlying pathology. Despite these observations there are so far no prospective studies to evaluate the clinical significance of CVL-dysfunction. Secondary aim 2 evaluates the relationship of CVL-dysfunction with OS and EFS. CVL-dysfunction may herald underlying undetected TE; the early diagnosis of which may prevent complications like overt TE, infection and therapy-delays. This in turn will improve the overall outcome in children with cancer.

#### Rationale for secondary aim 3

Although the three common complications of CVL namely CVL-dysfunction, infection and TE seem to be closely associated, the exact relationship is unclear. One retrospective study in children with cancer showed an increased risk of TE in association with CVL-dysfunction (OR 3.7, p = 0.001) and infection (OR 2.2, p = 0.016) whereas children having both dysfunction and infection had much higher risk of TE (OR 6.4, p<0.001) [17].

Presence of a local clot may lead to CVL-dysfunction as well as may act as a nidus of infection providing fertile ground for growth of the microorganisms. This may lead to either local, CVL-related infection or infection elsewhere in the body. CVL-dysfunction also needs frequent manipulations such as repeated attempts to infuse or withdraw blood; this may increase the chances of infection in immunocompromised patients. On the other hand, presence of infection can potentially initiate activation of coagulation and formation of TE in the vessel which is already damaged by CVL or by hyperosmolar infusions. The small clot developed in the process may progress to cause a significant TE either locally or distally elsewhere in the body. This clot may also lead to CVL-dysfunction.

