## Methods and design

This is a prospective analytical cohort study conducted at five tertiary care pediatric oncology centers in Ontario. Figure 2 outlines the research design of the study.

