##### Sample size

The primary objectives of the study are to develop a model to discriminate between patients with and without symptomatic TE. To determine the optimal discriminant clinical model we will undertake a multivariable analysis. Simulation studies demonstrate that logistic models require 10 to 15 events per predictor to produce stable model estimates [54,55]. Based on our retrospective data and published reports we anticipate that at least 20% patients will be exposed (i.e. with CVL dysfunction) and 80% unexposed (i.e. without CVL dysfunction) [17,33,36]. Preliminary data from the retrospective study showed that the overall prevalence of TE was 11%; 23% of exposed and 9% of unexposed patients had TE. We will evaluate five predictors in our multivariable analysis. In this study, we have a fixed sample size of 450 patients (90 exposed with CVL dysfunction; and 360 without CVL dysfunction). The overall rate of symptomatic TE is assumed to be 11% (~50 events of TE) [36].

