### Strengths and potential limitations of the study

The major strength of the study is the use of a prospective cohort design. Previous studies were single institution studies using retrospective design [17,32,33,36]. These studies report up to 30% of missing data [17,32,33,36]. To avoid this problem we will use uniform data collection forms for all study participants and for patients with TE which is likely to capture all the relevant information. Further, the CVL access data will be collected prospectively and hence the exposure criteria will be recorded properly avoiding any recall bias.

Unlike previous studies, evaluation of CVL-dysfunction is the primary aim of our study which formed the basis of our sample size calculation. By inclusion of only symptomatic and objectively confirmed TE, we will avoid ambiguity over diagnosis, and thus, reporting of TE. Uniform guidelines for diagnosis and evaluation will likely minimize chances of misdiagnosis of TE.

In addition the following steps are taken to minimize sources of errors and likely biases improving internal validity of the study. To avoid selection bias all consecutive newly diagnosed non-CNS cancer patients meeting the inclusion criteria will be eligible and approached for participation in the proposed study. All reported events of TE will be confirmed by an independent adjudication committee. To avoid recall bias CVL access data will be collected prospectively and hence the exposure criteria will be recorded properly. Assessors (radiologists) evaluating for TE will be blinded as regards the “exposure” status to avoid measurement bias. With the use of uniform data collection forms for all study participants and patients with TE, infection and CVL dysfunction, all the relevant information is likely to be captured. Further, all data will be analyzed centrally.

Another strength of the study is that this study is conducted across five pediatric oncology institutions with inclusion of wide range of cancer diagnoses. Hence we think that the findings of the study will be generalizable to pediatric oncology population. The results of this study will also be applicable for adults with cancer as well as to the population of patients with other chronic diseases who need long term CVL.

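### The OS and EFS hazard ratio is assigned to the log-rank method, which is unadjusted in its ordinary form, directly after Cox regression is chosen for its confounder adjustment

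*Protocol article*

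**What the plan says.** The survival analysis is set out in two adjacent sentences at the end of the Analysis plan in the protocol article. The first reads: "OS and EFS will be estimated using Cox-regression which will allow for adjustment of confounding variables". The second reads: "Hazard ratio (HR) will be calculated using log-rank method".

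These sentences serve secondary aim 2: "To compare the five-year OS and EFS in children with or without CVL-dysfunction". The design is observational: "This is a prospective analytical cohort study conducted at five tertiary care pediatric oncology centers in Ontario". The Strengths and potential limitations section counts among the study's strengths the "inclusion of wide range of cancer diagnoses". Age at diagnosis and type of cancer are both listed under Independent variables.

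Earlier in the Analysis plan, the sentence on reporting regression models names only one effect measure, the odds ratio for logistic regression. The log-rank sentence is therefore the only one that says where the hazard ratio comes from. It does not call that hazard ratio crude, supplementary or descriptive.

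**The concern.** The first sentence selects a model for its ability to adjust. The second takes the effect measure from a method that, as ordinarily used, compares two groups without covariates. Both cannot govern the same reported number.

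The conflict matters because exposure is not randomised. If children with some cancers have both more line dysfunction and worse survival, a crude hazard ratio will show an association even where dysfunction has no effect. The plan recognises this by asking for adjustment. Leaving two sources for the hazard ratio also leaves open, until the results are known, whether a crude or an adjusted value will be the headline.

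**Working it through.** **The plan's own figures.** The article gives no event count, survival rate or target hazard ratio for OS or EFS, so there is no survival figure to reproduce. The figures in its Sample size section concern thromboembolism, and they reproduce: 450 × 0.11 = 49.5, stated as about 50 events; 50 / 5 predictors = 10 events per predictor; 450 × 0.20 = 90 exposed, leaving 360 unexposed. None of them depends on the point made here.

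**What a log-rank hazard ratio is.** The two usual forms are (O₁/E₁)/(O₀/E₀) and exp[(O₁ − E₁)/V]. O and E are observed and expected events in the exposed (1) and unexposed (0) groups, and V is the variance of O₁ − E₁. Neither formula has a covariate term.

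**Hand illustration.** These inputs are assumptions, not taken from the documents: two cancer groups of equal size, five-year mortality 10% and 30%, constant hazards, no effect of dysfunction within either group. In both cases below, overall exposure averages 20%, as in the plan.

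- Five-year cumulative hazards: −ln(0.90) = 0.1054 and −ln(0.70) = 0.3567.
- Dysfunction in 15% and 25% of the groups. The exposed are 0.15/0.40 = 37.5% low-risk and 62.5% high-risk, with mean hazard 0.375 × 0.1054 + 0.625 × 0.3567 = 0.2624. The unexposed are 0.85/1.60 = 53.125% and 46.875%, with mean 0.2232. Ratio 0.2624 / 0.2232 = **1.18**.
- Dysfunction in 10% and 30%. The exposed mix is 25% and 75%, mean 0.2938. The unexposed mix is 56.25% and 43.75%, mean 0.2153. Ratio 0.2938 / 0.2153 = **1.36**.

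Within each cancer group the hazard ratio is 1.0, so the adjusted value is 1.0 in both cases.

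Averaging hazards is a shortcut, so the same cases were worked from five-year mortality. In the first, mortality is 22.5% in the exposed and 19.375% in the unexposed: −ln(0.775) / −ln(0.80625) = 0.2549 / 0.2154 = 1.18. In the second, it is 25% and 18.75%: 0.2877 / 0.2076 = 1.39. The result does not rest on the shortcut.

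**Simulation.** 450 patients (90 exposed, 360 unexposed), five years of follow-up, 400 runs per scenario. Assumed: one binary confounder present in 60% of exposed and 30% of unexposed patients, and a baseline hazard of 0.035 per year. Entries are geometric mean hazard ratios.

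| True HR | Confounder HR | Log-rank, O/E | Log-rank, exp[(O−E)/V] | Cox, unadjusted | Cox, adjusted |
|---|---|---|---|---|---|
| 1.0 | 1 | 0.98 | 1.01 | 0.98 | 1.00 |
| 1.0 | 2 | 1.21 | 1.25 | 1.21 | 0.98 |
| 1.0 | 3 | 1.36 | 1.42 | 1.36 | 0.98 |
| 1.5 | 1 | 1.43 | 1.52 | 1.43 | 1.43 |
| 1.5 | 2 | 1.87 | 2.15 | 1.87 | 1.54 |
| 1.5 | 3 | 2.03 | 2.42 | 2.04 | 1.51 |

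The O/E log-rank hazard ratio agrees with unadjusted Cox to within 0.01 throughout. It moves away from adjusted Cox once the confounder has an effect. An ordinary log-rank hazard ratio is, in practice, the crude Cox hazard ratio.

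**The case against.** The best reply is that the Cox sentence stands. A Cox model, once fitted, yields an adjusted hazard ratio, and nothing says that the log-rank value replaces it. The authors may have meant Cox for the hazard ratio and log-rank for the test, or a crude value beside the adjusted one. This reply stands in part. A reader might infer that the plan defeats adjustment, or that no adjusted hazard ratio will exist; the text does not support that. It does contradict itself on which number is the hazard ratio, and under any of these intentions the second sentence needs rewording.

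A reader might also infer that the study's stated aim is to show an independent effect, because the Rationale for secondary aim 2 says "our results suggest that CVL-dysfunction is an independent risk factor for poor OS and EFS in children with cancer". That sentence reports the investigators' earlier results. The secondary hypothesis and aim speak only of decreased survival and of comparing survival. The intention to adjust rests on the Cox sentence, which is enough for the inconsistency.

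Nor is it right that the log-rank approach can never adjust. A stratified log-rank handles categorical factors such as cancer type, though continuous age would first have to be grouped. The plan names no such version, so the statement holds for the ordinary form only.

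Finally, the illustrated rates are assumptions. They show what a crude hazard ratio can do, not what it will do in this cohort.

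**Conclusion.** The point holds as an internal contradiction about the effect measure for secondary aim 2, and it should be corrected. Taken literally, the designated hazard ratio is unadjusted. With no true effect it would be about 1.18 to 1.36 under the assumed mortality and exposure splits, against an adjusted value of 1.0. The documents do not allow the actual bias to be estimated.

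The primary logistic analysis and the fixed sample of 450 are untouched. A reader might extend the point to the fact that dysfunction arises during follow-up. The timing of exposure is a separate issue: a Cox model on ever/never dysfunction shares it, extended log-rank forms for changing exposure (Mantel-Byar) exist, and it is no part of this conclusion.

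**What to change.** Replace the log-rank sentence in the Analysis plan with:

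> The HR for CVL-dysfunction and its 95% CI will be taken from the Cox model adjusted for the pre-specified confounders (at least age and cancer type); the log-rank test will be used only as an unadjusted, descriptive comparison.

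Age and cancer type are already listed as independent variables, so no new data are needed. Any further covariates can be fixed in the statistical analysis plan. The cost is one sentence, with no change to sample size, significance level, data collection or procedures. The change should be made before survival outcomes are analysed, so that the choice between a crude and an adjusted hazard ratio is settled in advance.
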